# INVESTIGATIONAL MEDICINAL PRODUCT

## Name and description of investigational medicinal product

*Milgamma® mono 300*

Film coated tablets

Each tablet contains 300 mg benfotiamine

*Placebo*:

Film coated tablets

Each tablet contains microcrystalline cellulose instead of benfotiamine

## Summary of findings from non-clinical studies

Please see attached Summary of Product Characteristics, pages 2, 3

## Summary of findings from clinical studies

Pleae see attached Summary of Product Characteristics, pages 2, 3

## Summary of known and potential risks and benefits

Please see attached Summary of Product Characteristics, pages 2, 3, 4

## Description and justification of route of administration and dosage

The dose of the active study medication, benfotiamine, is chosen according to known clinical and experimental data.

For the treatment of diabetic polyneuropathy, daily doses up to 600 mg alone (33,35) or 320 mg in combination with pyridoxin (720 mg) and cyanocobalamine (2 mg) have been used (36-38).

The treatment of patients with type-II diabetes with 600 mg benfotiamine per day for 4 weeks leads to a reduction of CML (N-carboxmethyl-Lysin) in erythrocytes, a marker of intracellular oxidative stress (39). Similar results in patients with type-I diabetes have been shown in an open study too (40). Stirban et al. (41,42) used daily doses of 3x350 mg (1.050 mg) for 3 days to show that this dose significantly decreased vascular impairment after an AGE-rich meal in patients with type-II diabetes.

In diabetic rats, high oral doses of benfotiamine (7mg and 70mg per kg body weight) prevented the development of microalbuminuria by 70-80% (25). Furthermore, in another trial retinopathy in diabetic rats was prevented by high-dose benfotiamine (80 mg/kg body weight daily) (22).

Generally, it is accepted that lipophilic as well as water soluble thiamine derivatives have a very low toxicity and excellent tolerability. According to case reports, toxic effects of thiamine may occur after oral application of >3 g daily (43), which is higher than normal experimental or therapeutic dosage. Other case reports describe symptoms of a hyperthyroidism after doses of thiamine hydrochloride of 7g or 10g over 2 weeks (44,45). After discontinuation of thiamine hydrochloride, the symptoms resolved within 2 days. For benfotiamine no reports on overdose are known. In all clinical studies with benfotiamine performed up to now no serious adverse events have been observed. Only in single cases an allergic reaction may be possible. Therefore, patients with hypersensitivity to benfotiamine (or other constituents of the study medication, see SPC) should be excluded from the study.

## Dosages, dosage modifications and method of administration

*Dose and application interval:*

Treatment phase 1:

Group A: milgamma® mono 300 3x 1 film coated tablet daily (total 900 mg daily dose benfotiamine)

Group B: Placebo 3x 1 film coated tablet daily

*Route of administration:* Oral use

The pills should be swallowed without chewing with some fluid in the morning, at noon and in the evening. The intake is independent from meals.

## Preparation and labelling of Investigational Medicinal Product

Study medication containing benfotiamine corresponds to the approved drug milgamma® mono 300 (see SPC). Placebo is produced by the same manufacturer replacing benfotiamine by one of the other excipients (microcristalline cellulose).

For labelling of the study medication, see Attachment “Labelling”

## Drug accountability

The study medication is packed according to the randomization list by the manufacturer. For each patient, per treatment period an amount of 3x 100 film coated tablets are prepared. Each package contains 10 blisters of 10 film coated tablets.

After approval by the QP of the manufacturer, it is shipped to the clinic pharmacy of Isala Klinieken, Locatie Sophia. The pharmacy dispends the study medication to the investigator on request, who distributes the study medication to the patients.

After any treatment period, patients are asked to return the medication not taken or the empty package to the investigator. Rest medication is collected in the pharmacy of the clinic and sent back to Wörwag Pharma GmbH & Co. KG after end of the trial, where it is professionally eliminated.

# METHODS

## Study parameters/endpoints

### Main study parameter/endpoint

Change in urinary excretion of (measured in 24-hour urine):

• β2-microglobulin

• Albumin

### Secondary study parameters/endpoints

Change in urinary excretion of (measured in 24-hour urine):

• KIM-1 (kidney injury molecule-1)
• MIF (macrophage inhibiting factor)
• MCP-1 (monocyte chemo-attractant protein-1)
• C3d
• Urinary peptidomics
• Reactive oxygen species, advanced glycation end-products (AGEs), and carbonylated albumin

### Other study parameters

• Body Mass Index (BMI)

• Blood glucose

• HbA1c

• Blood urea nitrogen

• Plasma creatinine

• Blood thiamine

• Erythrocyte transketolase activity

## Randomisation, blinding and treatment allocation

The treatment phases of 3 months is performed in a double-blind design. Active medication and placebo have identical appearance and can be identified within this study only by the randomizing list.

A randomizing list will be prepared by [name]. [name] (independent statistician, University of Ulm, Germany) and sent to the manufacturer of the study medication for packaging. The randomizing list is to be stored strictly closed and must not be seen by anyone else than the packaging employee. After packaging, it has to be sealed and sent to Wörwag Pharma GmbH & Co. KG, where it is stored safe and strictly closed. A duplicate of the randomization list will also be stored in a safe by the statistician [name]. [name] for safety reasons, if the original list gets lost. After correct data unblinding by the original list, this duplicate list will be eliminated.

Additionally to the randomizing list for packaging of the study medication, two sets of sealed envelopes are prepared by the statistician for emergency purposes. Each envelope contains the allocation to the study medication for an individual patient. One set of sealed envelopes will be sent to the investigator, one set will be safely stored at Wörwag Pharma GmbH & Co. KG. If a serious adverse event occurs that requires the unblinding of a single patient, this will be performed by opening the envelope of this patient.

The reason for and the date of unblinding has to be documented on the envelope and in the CRF. All other patients remain blinded.

After the end of the study, all envelopes of the investigator have to be sent to the biometric centre. The integrity of the envelopes has to be documented by a third party.

## Study procedures

The patients will be instructed in advance how to collect the 24-hour urine in the previous day, and will be asked to refrain from food from the previous evening to take fasting blood samples

The subjects will visit the clinic 5 times during this clinical trial. Two times in the run in phase, one time directly before the beginning of the treatment phase, one time in the middle of the treatment phase, and one last time at the end of the treatment phase. They will be instructed in advance how to collect the 24-hour urine in the previous day, and will be asked to refrain from food from the previous evening to take fasting blood samples

In each visit the following procedures will be applied:

- Samples of 24-hour urine will be received from the patients and sent to the laboratory for analysis. The primary and secondary study parameters will be measured in the 24-hour urine of the preceding day.

- Second-morning urine samples will be collected and sent for analysis.

- Fasting blood samples will be drawn and sent for analysis.

- Weight and blood pressure will be measured.

- Compliance with the intake of the benfotiamine or placebo will be ensured by counting the pills in the last two visits of each patient.

## Withdrawal of individual subjects

Subjects can leave the study at any time for any reason if they wish to do so without any consequences. The investigator can decide to withdraw a subject from the study for urgent medical reasons.

### Specific criteria for withdrawal

- Serious adverse events
- Hospitalization of the patient
- Non compliance of the patient
- Change of concomitant medication which might influence the primary and secondary endpoints itself (e.g. ACE-inhibitors, AT II-antagonists)

## Replacement of individual subjects after withdrawal

Randomisation list, emergency envelopes and study medication will be prepared for 86 patients and another 86 patients for the case that the study goes on after interim analysis. If randomised patients are withdrawn from the study (drop-outs) then further patients will be admitted to the study until the scheduled sample size is achieved.

## Follow-up of subjects withdrawn from treatment

Subjects who withdraw from the study will be followed up according to the routine terms of care of diabetic patients attending in the clinic. Furthermore, any side effect or adverse reaction, which might or might not be a reason for withdrawal, will be reported and followed up carefully with the necessary actions.

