## Sample size calculation

The two primary outcome variables are quantitative. As primary outcome measure, the difference between the value at the end and the value at the start of medication is defined. It is assumed that the differences are normally distributed. P-values are adjusted for multiple testing by the Bonferroni-Holm-procedure. Hypotheses are one sided. As level of significance 2.5% are established.

It is proposed to have 38 evaluable patients per group. This sample size enables the study to detect an effect of size 0.65 with a power of 80%. Effect size is the difference in group means divided by the common standard deviation. For clarification: If (mean of the placebo group minus the mean of the verum group ) divided by the standard deviation is bigger or equal 0.65 then the study will deliver a significant result with a probability of at least 80%.

The drop-out rate is assumed to be 10%. Therefore 43 patients have to be randomised to each group to have 38 evaluable patients. For both groups together 86 patients are needed for admission to the study.

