### Suspected unexpected serious adverse reactions (SUSAR)

Adverse reactions are all untoward and unintended responses to an investigational product related to any dose administered.
Unexpected adverse reactions are adverse reactions, of which the nature, or severity, is not consistent with the applicable product information (e.g. Investigator’s Brochure for an unapproved IMP or Summary of Product Characteristics (SPC) for an authorized medicinal product).
The sponsor will report expedited the following SUSARs to the METC:

SUSARs that have arisen in the clinical trial that was assessed by the METC;

SUSARs that have arisen in other clinical trial of the same sponsor and with the same medicinal product, and that could have consequences for the safety of the subjects involved in the clinical trial that was assessed by the METC.

The remaining SUSARs are recorded in an overview list (line-listing) that will be submitted once every half year to the METC. This line-listing provides an overview of all SUSARs from the study medicine, accompanied by a brief report highlighting the main points of concern.

The sponsor will report expedited all SUSARs to the competent authority, the Medicine Evaluation Board and the competent authorities in other Member States and to Wörwag Pharma GmbH & Co. KG.

The expedited reporting will occur not later than 15 days after the sponsor has first knowledge of the adverse reactions. For fatal or life threatening cases the term will be maximal 7 days for a preliminary report with another 8 days for completion of the report.

For all events that may require the unblinding of participant treatment, the medical monitor must be contacted before the unblinding occurs. In all cases, the medical monitor will notify the protocol chairs and the medical officer.
Any treatment unblinding will require a full written account. The account will include the reason for unblinding the study medication, the name of the medical monitor notified of the unblinding, and the date and time of the unblinding. The reasons for unblinding each individual study treatment should be included on the Treatment Unblinding Case Report Form and in the final study report. If a participant is unblinded, study therapy is discontinued and the participant is terminated from the study.

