# STATISTICAL ANALYSIS

## Descriptive statistics

First, study patients will be described with their demographical and medical data. This will be done for the entire study population to describe study patients. Additionally this will be done separately for each of the two groups to investigate comparability of the groups (which might be disturbed due to drop-outs). Further, all outcome variables will be evaluated with descriptive statistical methods. For quantitative variables this includes maximum, median, mean, minimum as well as standard deviation. For qualitative variables absolute and relative frequencies will be used.

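### Patients withdrawn after randomisation have no planned week-12 urine and are replaced, so the primary outcome would probably exist only for those who were not withdrawn

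*Protocol*

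**What the plan says.** - **Grounds for withdrawal.** Section 7.4.1 lists serious adverse events, hospitalisation, "Non compliance of the patient", and changes of co-medication that could themselves move the endpoints. Section 8.2.1 adds: "If a participant is unblinded, study therapy is discontinued and the participant is terminated from the study".
- **Co-medication changes are treated differently elsewhere.** Section 5.2 lets a patient whose listed co-medication changes substantially either continue or be withdrawn.
- **Follow-up.** The heading of section 7.6 concerns withdrawal from treatment, but its text is about leaving the study: "Subjects who withdraw from the study will be followed up according to the routine terms of care of diabetic patients attending in the clinic". Side effects are also followed. No study visit or 24-hour urine is mentioned.
- **Replacement.** Under section 7.5, when randomised patients drop out, "further patients will be admitted to the study until the scheduled sample size is achieved". The same section prepares allocations for 86 patients, and for another 86 should the study go on after an interim analysis.
- **Outcome and size.** Section 9.2 compares the end-minus-start change in 24-hour urinary β2-microglobulin and albumin by a two-sample t-test. Section 4.4 sizes the trial on evaluable patients: "Therefore 43 patients have to be randomised to each group to have 38 evaluable patients".
- **Acknowledged risk.** Section 9.1 describes the groups separately in order to check "comparability of the groups (which might be disturbed due to drop-outs").

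**The concern.** Every listed ground for withdrawal arises after randomisation, so it can depend on the treatment or on the course of the disease. Changes in ACE inhibitors or angiotensin II antagonists are the clearest example. The introduction calls albuminuria reduction with these drugs the cornerstone of preventing progression, and section 7.4.1 names a change in them as a reason to withdraw. A patient whose albuminuria worsens is a natural candidate for such a change, and so for removal before the outcome is measured. That is an inference, but it follows from the protocol's own rationale.

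If such patients leave without a week-12 urine, the comparison is no longer between the groups as randomised. A newly admitted patient fills the place but does not stand in for the one who left. Unlike an analysis set or a missing-data method, this cannot be repaired later: the sample either was collected or was not.

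**Working it through.** **1. The plan's own figures.** Inputs from section 4.4: effect size 0.65, power 80%, 38 evaluable per group, 10% drop-out; "Hypotheses are one sided"; "As level of significance 2.5% are established".

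- Normal approximation: n = 2 × ((1.960 + 0.842)/0.65)² = 37.2, rounded up to 38 per group.
- Exact t-test power at 38 per group: 79.9%.
- Drop-out: 38/0.9 = 42.2, rounded up to 43 per group, 86 in total.

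The figures reproduce. The arithmetic is not the problem.

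**2. What a withdrawn patient contributes.** Sections 7.4.1 and 8.2.1 take the patient out of the study, section 7.6 plans routine care and safety follow-up, and section 9.2 needs an end-of-medication urine. Put together, a patient withdrawn before week 12 has no planned primary outcome. One withdrawn after the middle visit would have a week-6 value (sections 3 and 7.3).

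**3. Illustration of the bias.** Assumptions, none from the protocol except the 10%: no true effect; placebo drop-outs are a random sample of their arm; verum drop-outs, a share d, have a mean change k SD worse than their arm's mean. The verum patients who remain are then better than their arm's mean by

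b = d × k/(1 − d).

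With 38 remaining per group, the t-statistic has noncentrality b × √(38/2) and 74 degrees of freedom. The one-sided 2.5% critical value is 1.993.

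| d | k | b (SD) | b/0.65 | One-sided error, single test |
|---|---|---|---|---|
| 10% | 0.5 | 0.056 | 9% | 4.3% |
| 10% | 1.0 | 0.111 | 17% | 6.9% |
| 5% | 0.5 | 0.026 | 4% | 3.2% |
| 20% | 1.0 | 0.250 | 38% | 18.8% |

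The last two rows give the ends of the range for d from 5% to 20% and k from 0.5 to 1. The calculation holds the count at 38 per group, which is what replacement achieves, and the bias is still there.

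**4. How many are randomised.** Section 7.5 replaces until the scheduled size is reached but does not define that size. Section 4.4 offers 2 × 38 = 76 evaluable or 86 randomised. Under the first reading, the 86 allocations absorb 86 − 76 = 10 losses before any further number is needed. Under the second, any replacement goes beyond the first list. Past the first 86, the only numbers prepared are those reserved for continuation after an interim analysis.

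**5. Power if everyone is measured.** Exact t-test, 43 per group, one-sided 2.5%:

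- Effect stays 0.65: 84.6%.
- The 10% who stop have no benefit (assumption): effect 0.9 × 0.65 = 0.585, power 76.5%. For 80%, n = 2 × (2.802/0.585)² = 45.9, so 46 per group by the normal approximation.

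**The case against.** The best case on the other side has five parts.

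- **A reader might infer that the protocol rules out a week-12 urine after withdrawal, or fixes a completers-only analysis.** It does neither. Section 7.6 is silent about study samples, and section 9.2 names no analysis set. Analysis sets and missing-data methods commonly sit in an analysis plan, which is not at hand and could use week-6 values. This stands, and is why the point says *probably*. It does not remove the concern, because an uncollected sample cannot be planned back.
- **A reader might infer that replacements must use the reserved allocations, or that drop-out is counted twice.** Both depend on what the scheduled size means. If it is 76 evaluable, 43 per group is a forecast and replacement is the operating rule, needing extra numbers only after more than 10 losses. What remains is the missing definition.
- **Section 9.1 might be read as predicting imbalance.** It says only that drop-outs might disturb comparability, as the reason for a descriptive check.
- **Strong treatment-related withdrawal is not shown.** Section 6.5 reports no serious adverse events in earlier benfotiamine studies, and this is 12 weeks under blinding. Withdrawal after a drug change is also optional under section 5.2. Both are fair, and both bear on the size of the bias, which is unknown.
- **An on-treatment question is arguable in a short biomarker trial, and off-treatment values cost power.** Both stand. A secondary on-treatment set meets the first, and the second has to be stated openly.

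**Conclusion.** The concern holds in a limited form. The protocol merges stopping treatment with leaving the study, plans no study urine afterwards and replaces those who leave. Followed as written, it would probably leave the primary outcome available only for patients who were not withdrawn. That follows from what is planned; the protocol states no prohibition on later samples.

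Neither the size nor the direction of the bias can be derived from the document. The figures of 0.06 to 0.11 SD, and 4.3% to 6.9% error against 2.5%, rest on no true effect, the protocol's 10% drop-out, selection in the verum arm only, and an assumed gap of 0.5 to 1 SD. They describe a single test, before the Bonferroni-Holm adjustment.

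Two documentary defects go with it. The scheduled sample size in section 7.5 is undefined, and sections 5.2 and 7.4.1 differ on what follows a co-medication change and must be reconciled.

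**What to change.** 1. Leave the clinical rules on stopping tablets as they are, but state in sections 7.4 to 7.6 and 8.2.1 that stopping tablets is not the same as leaving the study.
2. Ask every randomised patient who has not withdrawn consent for the scheduled week-6 and week-12 24-hour urine, whatever has happened to tablets, co-medication or blinding.
3. Make the primary comparison as randomised, with an on-treatment set as secondary.
4. Delete the replacement sentence and fix the number randomised at 86.
5. Reconcile sections 5.2 and 7.4.1 on co-medication changes.

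**Cost.** Protocol wording, and one or two already scheduled collections for about nine patients (10% of 86 = 8.6). The real price is possible dilution. The allowance in section 4.4 is for missing patients, not for off-treatment values. With 43 per group measured, power is 84.6% if the effect stays 0.65 but 76.5% if the 10% who stop have no benefit. The sponsor should accept that risk knowingly when fixing 86; under that assumption, restoring 80% would take about 46 per group.

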## Premature termination of the study

The termination of the entire trial will be decided if a patient shows an unknown serious event that can be related to the study medication after thorough discussion. The decisions (individual or for the entire study) are taken by the sponsor and the investigators together.

# SAFETY REPORTING

## Section 10 WMO event

In accordance to section 10, subsection 1, of the WMO, the investigator will inform the subjects and the reviewing accredited METC if anything occurs, on the basis of which it appears that the disadvantages of participation may be significantly greater than was foreseen in the research proposal. The study will be suspended pending further review by the accredited METC, except insofar as suspension would jeopardize the subjects’ health. The investigator will take care that all subjects are kept informed.

## Adverse and serious adverse events

Adverse events are defined as any undesirable experience occurring to a subject during a clinical trial, whether or not considered related to the investigational drug. All adverse events reported spontaneously by the subject or observed by the investiga­tor or his staff will be recorded.
A serious adverse event is any untoward medical occurrence or effect that at any dose results in death;

- is life threatening (at the time of the event);
- requires hospitalization or prolongation of existing inpatients’ hospitalization;
- results in persistent or significant disability or incapacity;
- is a congenital anomaly or birth defect;
- is a new event of the trial likely to affect the safety of the subjects, such as an unexpected outcome of an adverse reaction, lack of efficacy of an IMP used for the treatment of a life threatening disease, major safety finding from a newly completed animal study, etc.

All SAEs will be reported to the accredited METC that approved the protocol, according to the requirements of that METC.

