**Nature and extent of the burden and risks associated with participation, benefit and group relatedness:**

-The patients are asked to attend the outpatient clinic for the study 5 times in total. Before each visit the patients are asked to collect a 24h urine sample. They will be asked to refrain from food from the previous evening to take fasting blood samples (5 vials of 7 ml). In addition, a second-morning urine sample will be collected.

- No other physical or physiological discomfort in association with participation is anticipated than the discomfort associated with the collection of the 24h urine samples and the blood sampling. There are no known risks associated with the investigational product other than the rare occurrence of urticaria and pruritus. In case of positive effects on diabetic nephropathy (albuminuria) a program on prophylaxis and treatment of diabetic nephropathy with benfotiamine will be taken into account. Benfotiamine will be investigated to assess its effect on markers of tubulointerstitial damage and inflammation associated with diabetic nephropathy. If it will be demonstrated that benfotiamine causes an improvement in these markers, the drug may become eligible for further large studies on its efficacy in prevention of the development of end-stage renal disease in susceptible diabetic patients. Participation of diabetic nephropathy patients in this study is of great importance, and answering the questions of this clinical trial is not possible without observing and analyzing the parameters at the end of the study.

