***Treatment phase (12 weeks):***

After the patients are randomly divided into two groups, the treatment is given for both groups for 12 weeks in a double-blind pattern. One group will be given the study medication, and the other will be given the placebo.

During this phase patient are asked to attend the outpatient clinic 2 times:

*-Week 0 (the beginning of the phase)*

*-Week 6*

*-Week 12 (the end of the phase)*

In each visit of these, fasting blood samples (5 vials of 7 ml) are drawn for analysis (blood glucose, HBA1c, and other parameters), second-morning urine sample is collected, and 24-hour urine (of the preceding day) is sent to the laboratory for analysis.

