### Annual safety report

In addition to the expedited reporting of SUSARs, the sponsor will submit, once a year throughout the clinical trial, a safety report to the accredited METC, competent authority, Medicine Evaluation Board and competent authorities of the concerned Member States.

This safety report consists of:

- a list of all suspected (unexpected or expected) serious adverse reactions, along with an aggregated summary table of all reported serious adverse reactions, ordered by organ system, per study;

- a report concerning the safety of the subjects, consisting of a complete safety analysis and an evaluation of the balance between the efficacy and the harmfulness of the medicine under investigation.

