## Recruitment and consent

Subjects will be invited to participate in the study by sending letters to them, in which they will find a full explanation of the study, advantages and disadvantages of participating, and contact information of the research team members working on this study. Moreover, the letter contains contact information of independent physician, to whom subjects can address questions about the research before, during and after a study. The letter will be sent by the supervising doctor [name]. [name], internist nephrologist, and the patients will be given 2 weeks to consider their decision. The subjects are asked then to sign their written informed consent before they take part in the study. Furthermore, the patients will be requested to sign separate informed consents concerning their permission on storing small quantities of collected 24-hour urine (10 ml) and withdrawn blood (3 ml), in order to perform possible further laboratorial analyses which are not available at the current time or may turn out to be interesting (regarding diabetic nephropathy) in the frame of this research in the future. These materials will be stored in -80 ºC freezers at Isala Klinieken hospital in Zwolle. The permission of the medical ethical committee (METC) Zwolle will be requested before performing any of these possible laboratorial investigations. The general practitioners (Huisartsen) will be informed about the participation of their patients.

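### Section 8.2 commits to recording adverse events that are volunteered or observed and names no question to patients, so minor symptoms may be under-recorded to an unknown extent

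*Protocol*

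**What the plan says.** Section 8.2 of the Protocol defines an adverse event broadly: any undesirable experience during the trial, related to the drug or not. The recording rule that follows names two routes: "All adverse events reported spontaneously by the subject or observed by the" investigator or his staff.

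Section 7.3 introduces its visit list with "In each visit the following procedures will be applied". The items are 24-hour urine, second-morning urine, fasting blood, "Weight and blood pressure will be measured", and a pill count at the last two visits. For weeks 0, 6 and 12, section 3 says "In each visit of these, fasting blood samples (5 vials of 7 ml) are drawn for analysis" and adds the two urine samples. Neither list mentions a question about complaints.

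Three other places bear on the point:

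- The Summary says the product has no known risks "other than the rare occurrence of urticaria and pruritus".
- Section 10.2 says the invitation letter gives patients "contact information of the research team members working on this study".
- Section 7.6 commits to reporting and following up any side effect in patients who withdraw, whether or not it caused the withdrawal.

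Section 8.2.2 requires an annual report that includes "a complete safety analysis and an evaluation of the balance between the efficacy and the harmfulness of the medicine under investigation".

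**The concern.** The definition of an adverse event is wider than the stated way of finding one. Staff will see an abnormal laboratory value, a raised blood pressure or a hospital admission. They will not see itching, or a rash that comes and goes between visits six weeks apart. Such events enter the data if the patient thinks to mention them.

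What is at stake is how to read a low or zero count of a minor symptom. With volunteered reporting, few events and few reports look alike. This has some weight here because patients take 900 mg a day for 12 weeks. The type 2 diabetes experience described in section 6.5 is 600 mg a day for 4 weeks and 1,050 mg a day for 3 days, so the trial should add tolerability information at a high sustained dose. An analysis plan cannot recover symptoms that were never written down, so the matter belongs in the protocol.

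**Working it through.** **The text, read across sections.**

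| Place in the Protocol | What it provides | Enquiry about complaints? |
|---|---|---|
| 8.2, recording rule | Spontaneous report or staff observation | None named |
| 7.3, visit list | Urine, blood, weight, blood pressure, pill count | None listed |
| 3, treatment phase | Blood and urine at weeks 0, 6 and 12 | None listed |
| 7.1, endpoints and parameters | Urinary markers, BMI, blood tests | Adverse events not listed |
| 7.6, withdrawn patients | Side effects reported and followed up | No routine question described |
| 8.3, follow-up of events | Follow-up until abated or stable | Concerns events already known |

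**Number of patients.** Section 4.4 states that "43 patients have to be randomised to each group". This reproduces: 38 evaluable patients divided by (1 − 0.10) is 42.2, rounded up to 43.

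**Assumptions.** The Protocol gives neither the rate of any symptom nor the share of symptoms that patients volunteer. Call that share s, with a range of 100%, 90%, 75% and 50%. Each affected patient is taken to be captured independently with probability s.

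**Upper bound after zero recorded cases.** With true rate p and n = 43, the chance of recording none is (1 − p·s)^43. Setting this to 0.05 gives the one-sided 95% upper bound:

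p = (1 − 0.05^(1/43)) / s = 0.0673 / s

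**A commoner symptom.** For an assumed true rate of 10%, the expected recorded count is 43 × 0.10 × s = 4.3·s, and the chance of recording none is (1 − 0.10·s)^43.

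| Captured share s | Upper bound after zero cases | Expected recorded count at a 10% rate | Chance of recording none at a 10% rate |
|---|---|---|---|
| 100% | 6.7% | 4.3 | 1.1% |
| 90% | 7.5% | 3.9 | 1.7% |
| 75% | 9.0% | 3.2 | 3.5% |
| 50% | 13.5% | 2.2 | 11.0% |

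**How much a question could gain.** The first row is a ceiling, because one question every six weeks will not capture everything. If a question raised capture from 50% to 75%, say, the bound would fall from 13.5% to 9.0%, not to 6.7%.

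**A very rare reaction.** The Protocol puts no figure on rare. For an assumed rate of 0.1%, the expected count in 43 patients is 43 × 0.001 = 0.043 with complete capture and about 0.02 with half. The chance of recording at least one case is 1 − 0.999^43 = 4.2% against 1 − 0.9995^43 = 2.1%. Either way the arm will most likely show none, and a question changes little.

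**The case against.** The strongest case against has four parts.

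1. **The rule is not exclusive.** A reader might infer that events are recorded only if volunteered or observed, or that nobody will ask. The text supports neither. Section 8.2 says that volunteered and observed events will be recorded; it rules out no other route. This stands, and the point is limited to what is named and listed.

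2. **The visit list is weak evidence.** Section 7.3 leaves out tasks that the Protocol requires elsewhere: documenting changes of concomitant medication (section 5.2) and handing out study medication (section 6.8). A list with those gaps cannot show that no enquiry takes place. A CRF exists and is not shown; it may contain the question. This also stands. Even so, such a CRF would go beyond a protocol rule that speaks of spontaneous reporting, which is itself a reason to align the text.

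3. **Other routes exist.** Patients can mention past symptoms at any visit, they have the team's contact details, and section 7.6 covers those who withdraw. These reduce the loss. They do not amount to a routine question for patients who stay in the trial.

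4. **No planned inference changes, and the sizes are hypothetical.** Adverse events are not a listed endpoint, and section 9 plans no specific comparison of them. At 75% to 90% capture, the chance of missing a 10% symptom altogether rises only from 1.1% to between 1.7% and 3.5%. For reactions as rare as the two named in the Summary, a question would add little. All of this stands. What remains is the interpretability of commoner, milder complaints in the safety report of section 8.2.2.

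**Conclusion.** The point holds as an optional improvement, with medium confidence. Section 8.2 states a weaker way of finding events than it needs to, and no listed visit procedure makes up for it. Non-serious, symptom-only events may be under-recorded, by an unknown amount.

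The illustrative size is an upper bound of 7.5% to 13.5% after zero recorded cases in 43 patients, against 6.7% with complete capture. It rests on assumed capture shares of 90% down to 50%, and it overstates what a question would recover.

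A reader might go further and infer that the safety comparison is biased in favour of benfotiamine. The documents do not support that: the same rule applies to both arms, and section 7.2 provides double blinding with tablets of identical appearance. Nor is there any effect on serious events, laboratory results, the two primary endpoints or the power of the trial.

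**What to change.** In section 8.2, extend the recording rule to events reported in answer to one standard, non-leading question on new complaints, asked identically of all patients at weeks 0, 6 and 12, with the answers recorded as adverse events. Add the same question to the visit list in section 7.3. The week 0 answer, taken before treatment, gives a baseline against which later complaints can be read.

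The cost is one CRF question at three visits that already take place. The downside is more minor background events to record in both arms. Dose, visit schedule, sample size and analysis stay as they are. If the CRF already contains such a question, only the wording of the Protocol needs to change.
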